### Sample size calculation

As no studies in the field of nursing care have investigated the effects of aftercare in addition to a supportive intervention for carers, the sample size calculation for this study is based on the current results of the evaluation study on the effectiveness of the rehab program for family carers of people with dementia without aftercare (“standard care”), upon which this study project is based [11], and the results of a 2012 study of the impact of individualized aftercare on long-term rehab effects [18].

In the study with family carers, six months after rehab ended, the outcome parameter of participation, which was captured with the Index for the Measurement of Restrictions on Participation (Index zur Messung von Einschränkungen der Teilhabe, IMET [19]), showed that the rehab effect had nearly completely disappeared (ES = 0.06).

In the rehab aftercare study for the indication lower back pain, the same effect was observed for participation (IMET) in the CG [18], while the rehabilitants of the IG with individualized aftercare still showed an approximately medium effect size after 12 months (ES = 0.44).

Due to the consistently strong effects at the end of rehab in most recorded outcomes in the evaluation study for the rehab program in Ratzeburg, we expect for this controlled study, with telephone-based aftercare at the 6-month follow-up, an average effect of ES = 0.5 in the IG and a small effect of ES = 0.06 in the CG. Using a test power of 80% as the base, a two-sided t-test with an alpha error level of 5% requires a net group size of *N* = 82 each for the IG and CG. Based on experience with the current evaluation study of the rehab program in Ratzeburg and due to the high degree of loyalty of the rehabilitants to the rehab facility, we assume a moderate dropout rate of 20%. To evaluate *N* = 82 rehabilitants per group, initially, 103 participants per study group should be included. The rehab centre treats between 210 and 330 carers per year. The required number of cases can thus be achieved within the envisaged recruitment time.

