#### Secondary outcomes

Depressed mood states are measured with the German version of CES-D, which contains 20 quadruple scaled items. The presence and frequency of depressive symptoms are thus tested for. The evaluation is performed through a sum score, which can reach a maximum value of 60 points. A higher value describes a stronger expression of depressive symptoms. Good reliability and validity are reported [27].

For the general complaints, the subscale of somatization from the Symptom Checklist by Franke (SCL-90R) is used. This scale captures subjective impairment due to physical complaints via 12 five-fold stepped items. High values indicate high impairments. The reliability and validity of the scale have been proven [28].

The WHOQOL-BREF is used to assess the generic subjective perceived quality of life of the family carers. It contains 26 items on four dimensions; high values indicate a high quality of life. It is a valid and reliable cross-indication measuring instrument for assessing the quality of life [29, 30].

The extent of social support is assessed with the questionnaire for social support (FSozU K22). It contains 22 items; high values indicate a high level of social support. High reliability and validity have been proven [31].

Performance in the areas of life, everyday life, leisure and job, are captured on three numerical scales ranging from 0 to 10, with high values indicating high performance. In routine data collection, the three items have been proven to be a valid method of determining performance limitations [32, 33].

The utilization of support services will be recorded by single items used in a recent study on the rehab of carers. There will be standardized queried, inter alia, nursing service, self-help groups, household help, pastoral care and use and type of other offerings.

Moderator variables, risk factors [34] and socio-demographic variables [35] will also be recorded.

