### Data analysis

#### Effect analysis

For the effects analysis of the longitudinal data, analysis of variance with repeated measurements is used; for nominal and ordinal scaled parameters, contingency table analyses are used; and for subgroup analyses, chi-square tests and t-tests are used. The analyses are performed with SPSS 22.0 and complete cases will be analysed.

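### As worded, the analysis of nominal and ordinal outcomes makes no use of the t0 answer; a t0-adjusted model would be a free gain for the support-offer items

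*Protocol article*

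**What the plan says.** The Effect analysis section splits the outcomes by type. For scores it states: "For the effects analysis of the longitudinal data, analysis of variance with repeated measurements is used". For the rest: "for nominal and ordinal scaled parameters, contingency table analyses are used". It adds that "for subgroup analyses, chi-square tests and t-tests are used", and closes with "The analyses are performed with SPSS 22.0 and complete cases will be analysed". For the nominal and ordinal outcomes it names no test statistic, no stratification, no trend test and no role for the baseline answer.

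The outcome mainly concerned is support offers, which Table 1 lists as secondary. The Secondary outcomes section says: "The utilization of support services will be recorded by single items used in a recent study on the rehab of carers". Its examples are nursing service, self-help groups and household help. Response formats are not given, but use of a service is most naturally a yes/no or nominal answer. Table 1 marks these items at t0 and in its last two columns, read here as the 6- and 12-month follow-ups.

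**The concern.** Whether a carer already used a service at t0 is likely to predict whether they use it later. A table of arm against follow-up answer ignores that. It then has less power than a comparison within t0 users and t0 non-users, and any chance difference in t0 use between arms passes into the follow-up comparison. It also does not show who took up a service they had not used before. That question matters here: the Intervention section has the groups work on the aftercare recommendations and on social networks, while controls may use local services freely.

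For an item with ordered categories there is a second possible loss, because an ordinary chi-square treats the categories as unordered.

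At stake is the efficiency and readability of secondary results, not the validity of the trial.

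**Working it through.** **1. The plan's own sample size.** Sample size calculation assumes "an average effect of ES = 0.5 in the IG and a small effect of ES = 0.06 in the CG", a difference of 0.50 − 0.06 = 0.44 SD, with 80% power and two-sided 5% alpha. The normal formula gives 2 × (1.96 + 0.8416)² / 0.44² = 81.1, so 82 per arm. An exact t-test gives 82.05, with power 0.80 at 82. With 20% dropout, 82 / 0.8 = 102.5, so 103. Both figures reproduce. Because complete cases are analysed, 82 per arm is used below.

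**2. Yes/no item: the cost of ignoring t0.** From the documents: 82 per arm. Assumed: 40% use at t0; control-arm follow-up use *a* among t0 users and *b* among t0 non-users; odds ratio 2.5 for the intervention within each t0 group.

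Formulas, where q0 and q1 are the overall follow-up proportions in control and intervention:
- phi = (a − b) × √(0.4 × 0.6) / √(q0(1 − q0))
- Plain table: z = (q1 − q0) / √(2p̄(1 − p̄)/82), with p̄ the mean of q0 and q1
- Stratified by t0 (Mantel-Haenszel): z = Σ w·d / √(Σ w·m(1 − m)), where each t0 group has w = 82f/2, f its share, d the difference between arms and m the mean proportion
- Power = Φ(z − 1.96)

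Worked case, a = 0.85, b = 0.20:
- q0 = 0.4 × 0.85 + 0.6 × 0.20 = 0.46, and phi = 0.65 × 0.490 / 0.498 = 0.64.
- With odds ratio 2.5, 0.85 becomes 0.934 and 0.20 becomes 0.385, so q1 = 0.604.
- Plain table: z = 0.144 / 0.0779 = 1.85, power 46%.
- Stratified: w = 16.4 and 24.6; Σ w·d = 5.92; Σ w·m(1 − m) = 6.67; z = 5.92 / 2.58 = 2.29, power 63%.

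| a / b | phi | Plain table | Stratified by t0 | Gain (points) |
|---|---|---|---|---|
| 0.85 / 0.20 | 0.64 | 46% | 63% | 17 |
| 0.80 / 0.20 | 0.59 | 51% | 66% | 15 |
| 0.70 / 0.30 | 0.39 | 70% | 76% | 6 |
| 0.60 / 0.35 | 0.25 | 77% | 79% | 2 |
| 0.55 / 0.40 | 0.15 | 80% | 81% | 1 |

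Simulation with 20,000 trials per row agrees within about one point (46/64, 51/67, 70/76, 78/80, 80/81). With no effect, both tests reject in about 5% of trials.

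A different model gives a similar picture. A latent normal variable split in half, with a 0.44 SD shift and 3,000 runs per setting, gives gains of about 2 points (59.0% to 61.1%), 5 points (59.6% to 64.4%) and 12 points (58.7% to 71.2%) at latent correlations of 0.3, 0.5 and 0.7.

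**3. Chance imbalance.** The standard error of the difference between arms in t0 use is √(2 × 0.4 × 0.6 / 82) = 0.077. With a − b = 0.65, an imbalance of that size moves the follow-up difference by 0.65 × 0.077 = 0.05, against a true difference of 0.144 in the worked case. It averages to zero over randomisations, so this is noise rather than bias.

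**4. Ordinal item: the cost of ignoring order.** Assumed: equally likely categories, a 0.44 SD latent shift (the IMET assumption, borrowed) and 82 per arm. Unordered chi-square against trend test, with no use of t0:
- 3 categories: 59% against 69%, a loss of about 10 points
- 4 categories: 57% against 74%, about 17
- 5 categories: 53% against 75%, about 22

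With two categories the two tests coincide and nothing is lost.

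**The case against.** The strongest counter-argument is that the phrase covers a family of methods. Linear-by-linear trend tests and Mantel-Haenszel tests stratified by t0 are themselves contingency-table analyses, so the better comparator in step 2 is one reading of the plan. A reader might infer that the plan prescribes an unstratified Pearson chi-square and so throws away both the t0 answer and the ordering. The text does not support that: chi-square is named only for subgroup analyses, and the wording permits the loss without stating it. The choice of statistic could also sit in a fuller document that is not shown.

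A reader might also merge steps 2 and 4 into one range of lost power for the trial's categorical outcomes. That would be wrong. The two losses concern different kinds of item, and no named outcome with a t0 value is clearly ordinal. The performance scales are described as numerical, 0 to 10. The five-level items belong to the process evaluation, and Table 1 shows no t0 value for them. If the support-offer items are yes/no, the ordering loss does not arise.

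The baseline association may also be weak, since t0 precedes the rehab and both arms receive aftercare recommendations. The gain could then be as small as 1 to 3 points.

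What remains is that the article contrasts a repeated-measures method for scores with a table method for categorical outcomes, and gives the collected t0 answer no role in the latter. A concrete, better method is available without new data.

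**Conclusion.** The point holds as a minor, cost-free improvement to the analysis of secondary outcomes. As worded, the plan makes no use of the t0 answer for nominal and ordinal items. If a plain follow-up table is meant, the yes/no support-offer items give up between about 1 and 17 points of power, depending almost entirely on how strongly t0 use predicts later use. That range rests on assumed t0 use, follow-up use and odds ratio, none of which the documents give. The further loss of roughly 10 to 22 points applies only to an item that is truly ordinal and is tested by an unordered chi-square, again under assumed category counts and shift. Type I error stays near 5%, the comparison is not biased, and the IMET analysis and its 80% power are unaffected.

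**What to change.** Replace the contingency-table comparison of arms with regression on arm and the t0 value of the same item: logistic for yes/no items, proportional-odds for ordinal items. Report an odds ratio with 95% CI at 6 and at 12 months, and state that it is conditional on the t0 answer; it will differ from a crude odds ratio (in the worked case 2.5 against (0.604/0.396)/(0.46/0.54) = 1.79). For multi-category nominal items, or where cells are sparse, use a Mantel-Haenszel test stratified by t0 use, in its generalised form where there are more than two categories. Keep cross-tabulations as description, split by t0 use so that new uptake is visible.

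The cost is a few lines of analysis wording. The t0 items are already collected and SPSS fits both regression models. Check that the generalised Mantel-Haenszel test is available in the named version. No participants, visits or data are added.

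### The tests named for subgroup analyses, t-tests and chi-square tests, cannot show whether the aftercare effect differs between subgroups

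*Protocol article*

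**What the plan says.** The Effect analysis section of the protocol article gives each kind of analysis its own method. For the main analysis: "For the effects analysis of the longitudinal data, analysis of variance with repeated measurements is used". For subgroups: "for subgroup analyses, chi-square tests and t-tests are used". The analysis set is also fixed: "complete cases will be analysed".

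Table 1 has a block of moderator variables (height, weight, smoking, socio-demographic data), and the Secondary outcomes section adds: "Moderator variables, risk factors [34] and socio-demographic variables [35] will also be recorded". The article names no subgroups and does not mention a treatment-by-subgroup interaction. The sample size calculation covers only the overall comparison of the two arms.

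**The concern.** A moderator is a variable on which the size of the treatment effect depends. To show moderation, the effect (intervention minus control) in one subgroup has to be compared with the effect in another. A two-sample t-test or a chi-square test on a two-way table does not do this, whichever way it is used:

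- **Arms compared within each subgroup.** Each test sets one subgroup's effect against zero. A significant result in one subgroup and a non-significant result in the other is not evidence that the two effects differ.
- **Subgroups compared with each other.** The test shows whether outcomes differ by type of carer. That may be a prognostic difference with no bearing on the treatment effect, even when only the intervention arm is examined, because nothing is subtracted for the control arm.

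At stake is a false statement that the aftercare works for one kind of carer and not for another, or a true difference that is never properly estimated. The named method is open to this because each subgroup holds only part of a sample that was sized for the overall effect.

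**Working it through.** **Inputs from the Sample size calculation section**
- Expected effects: "an average effect of ES = 0.5 in the IG and a small effect of ES = 0.06 in the CG", so the difference is 0.50 − 0.06 = 0.44 SD.
- Test, power and alpha: "Using a test power of 80% as the base, a two-sided t-test with an alpha error level of 5% requires a net group size of" "82 each for the IG and CG".
- Dropout: "we assume a moderate dropout rate of 20"%, with 103 recruited per arm.

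**Assumptions, not in the documents**
- One two-level subgroup factor, split equally (41 + 41 per arm). Splits up to 80:20 are shown.
- The same true effect in both subgroups: 0.44 SD, with 0.20 to 0.50 SD shown.
- Arms compared within each subgroup by a two-sided 5% t-test, and the results read side by side.

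**Step 1. The plan's own figures reproduce.** n = 2(1.96 + 0.8416)² / 0.44² = 81.1, rounded up to 82 per arm. The noncentral t gives power 0.7997 at 82 per arm. Recruitment: 82 / 0.80 = 102.5, rounded up to 103.

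**Step 2. Power within one subgroup.** With 41 per arm, the noncentrality is 0.44 / √(2/41) = 1.99 and power is 0.503.

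**Step 3. Chance that exactly one subgroup is significant although the effects are equal.** The subgroups contain different people, so P = p₁(1 − p₂) + p₂(1 − p₁). At an equal split this is 2 × 0.503 × 0.497 = 0.50. The other outcomes are both significant (0.25) and neither significant (0.25).

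| Uniform effect | Split | Per arm | Power in each | Exactly one significant |
|---|---|---|---|---|
| 0.44 SD | 50:50 | 41 / 41 | 0.503 / 0.503 | 0.50 |
| 0.44 SD | 60:40 | 49 / 33 | 0.578 / 0.421 | 0.51 |
| 0.44 SD | 70:30 | 57 / 25 | 0.644 / 0.332 | 0.55 |
| 0.44 SD | 80:20 | 66 / 16 | 0.708 / 0.226 | 0.61 |
| 0.20 SD | 50:50 | 41 / 41 | 0.146 / 0.146 | 0.25 |
| 0.30 SD | 50:50 | 41 / 41 | 0.269 / 0.269 | 0.39 |
| 0.50 SD | 50:50 | 41 / 41 | 0.609 / 0.609 | 0.48 |
| 0.50 SD | 80:20 | 66 / 16 | 0.814 / 0.278 | 0.64 |

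**Step 4. The interaction test on the same data.** In 100,000 simulated trials with a uniform effect of 0.44 SD, the group-by-subgroup test was significant in 0.050 (both at 50:50 and at 70:30). The side-by-side reading was discordant in 0.50 and 0.55. Among trials with a significant overall result, it was discordant in 0.57 and 0.64.

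**Step 5. What the interaction test can detect.** With four cells of 41, the standard error of the difference between two subgroup effects is √(4/41) = 0.312 SD. For a true difference in effect of 0.44 SD, 0.44 / 0.312 = 1.41, and power is Φ(1.41 − 1.96) = Φ(−0.55) = 0.29.

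**The case against.** The strongest reply is that a great deal is being read into one clause of a condensed article whose analysis plan is not shown. The clause does not say which groups are compared, on which outcome, or how the results will be read. The research questions ask nothing about differential effects, and nothing ties the moderator variables to the subgroup analyses. The tests might even be meant only for description. Definitions of subgroups and model terms are commonly left to the full plan.

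Much of this stands, and it limits the point. It does not remove it, because the article names the tests, and under either use they do not test effect modification. That is a stated choice of method and not a missing detail.

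A reader might infer more than the documents support:

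- **That the plan rejects interaction tests.** It never mentions them, and the repeated-measures ANOVA in the same sentence could carry a subgroup factor.
- **That the subgroup tests ignore baseline.** A t-test can be run on change scores, and the article does not say which scores are used.
- **That subgroup results would decide who is offered the aftercare.** The Discussion speaks of establishing the offer at the clinic and extending it to other carers and indications, not of restricting it.
- **That the number of tests is itself an argument against t-tests.** With no effect at all, three binary moderators (an illustrative number) mean six within-subgroup tests and, treated as independent, 1 − 0.95⁶ = 26% with at least one false positive. Three interaction tests would still give 1 − 0.95³ = 14%. This supports a short list, not one test over the other.

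**Conclusion.** The point holds in a limited form. The tests fixed for subgroup analyses cannot answer whether the aftercare effect differs between subgroups.

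If arms are compared within subgroups and significance is read side by side, a uniform effect would look like a differential one in about half of trials at the planned effect and an equal split. The figure runs from about 25% to 64% over splits of 50:50 to 80:20 and effects of 0.20 to 0.50 SD, against about 5% for an interaction test. These percentages rest on that reading and on an assumed split. They do not apply if subgroups are compared with each other, but that comparison does not test effect modification either.

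The matter concerns secondary, exploratory analyses. The primary comparison and its sample size are unaffected.

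**What to change.** Replace the subgroup clause in the Effect analysis section with wording to this effect:

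- Any claim that the effect differs between subgroups rests on an interaction term. In the planned repeated-measures ANOVA this is group-by-time-by-subgroup, or group-by-subgroup where a single time point is analysed. For categorical outcomes it is the group-by-subgroup term in a logistic model.
- The three-way term has several components when there are more than two time points, so the contrast to be reported should be named. The 6-month contrast matches the sample size calculation.
- The moderators are a short list fixed before the data are analysed.
- For each, the interaction estimate with its 95% CI and the subgroup effects from the same model are reported, labelled exploratory.
- A non-significant interaction is not to be taken as proof of a uniform effect, because power is only about 29% even for a 0.44 SD difference in effect with 41 per cell.

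T-tests and chi-square tests can stay for purely descriptive comparisons. The cost is a change of wording and a few extra model terms. No further data, visits or participants are needed. The price is that the interaction estimates will be imprecise, which the confidence intervals will show.

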## Methods

### Design

To investigate the long-term effects of telephone-based aftercare groups, a randomized controlled prospective longitudinal study is being conducted at one rehab centre. For the effect and process evaluation, in the sense of a mixed-method approach, both quantitative and qualitative methods are used [17]. Rehabilitants receive specific rehab for family carers of people with dementia and are randomized at the end of the measure. The randomization is performed externally by the Institute for Social Medicine and Epidemiology (ISE) of the University of Lübeck by generating a randomization list with the statistics program SPSS 22.0. After the rehab, at six appointments and in addition to the aftercare recommendations by the social worker, the intervention group receives telephone-based aftercare in groups, and the control group receives only the aftercare recommendations. The study design includes four measurement times: at the beginning (t0), at the end of the rehab (t1), 6 months after the end of the rehab (for the IG after completion of telephone-based aftercare groups) (t2) and 12 months after rehab ends (t3). Figure 1 represents the study flow.

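### Complete-case repeated-measures ANOVA with 20% expected dropout can discard observed 6-month IMET values and bias the effect if outcome-related loss differs by arm

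*Protocol article*

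**What the plan says.** The Effect analysis section of the protocol article names repeated-measures analysis of variance for the longitudinal outcomes and fixes the handling of missing data: "The analyses are performed with SPSS 22.0 and complete cases will be analysed". It mentions no other analysis set or method for missing values.

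The Sample size calculation section expects loss: "we assume a moderate dropout rate of 20" per cent. It assumes "an average effect of ES = 0.5 in the IG and a small effect of ES = 0.06 in the CG", "with telephone-based aftercare at the 6-month follow-up". The net requirement is "82 each for the IG and CG", and to reach it "initially, 103 participants per study group should be included". The dropout sentence gives no time point.

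Under Design, "The study design includes four measurement times": start of rehab, end of rehab, and 6 and 12 months after rehab. Table 1 marks the primary outcome, IMET, at baseline and the two follow-ups, with no mark at the end of rehab. (Table 1 labels the last two columns t3 and t4, while Design calls these occasions t2 and t3. They are read here as 6 and 12 months.)

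**The concern.** Classical repeated-measures ANOVA on complete cases deletes listwise: a carer needs a value at every occasion in the model. For IMET with both follow-ups in the model, that means baseline, 6 and 12 months. A carer who returns the 6-month form but not the 12-month form then drops out of the 6-month contrast as well, although that value is in hand and 6 months is the time point behind the sample size.

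Reasons for not returning a form could differ by arm. The intervention group has six sessions at four-week intervals, a reminder call before each, and an evaluation form after each. The control group receives a portfolio of recommendations and no accompanying aftercare. If the carers lost from one arm differ in outcome from those lost from the other, the carers who remain are no longer comparable, and the estimated effect on the primary outcome shifts.

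**Working it through.** **Inputs from the protocol article (Sample size calculation).** Two-sided t-test, alpha 0.05, power 80%; effect sizes 0.5 (IG) and 0.06 (CG), so d = 0.5 - 0.06 = 0.44 SD; dropout 20%; 82 net and 103 enrolled per arm.

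**Step 1: reproduce the plan's figures.**
- n per arm = 2 × (z0.975 + z0.80)² / d² = 2 × (1.960 + 0.842)² / 0.44² = 81.08, rounded up to 82.
- The noncentral t-test with 82 per arm has 79.97% power.
- Enrolment = 82 / (1 - 0.20) = 102.5, rounded up to 103.

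Both stated figures reproduce.

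**Step 2: how many carers leave the comparison.** 103 × 0.8 = 82.4, so 82 remain. 103 - 82 = 21 per arm, or 42 of 206 randomised, are expected to be left out.

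**Step 3: bias (illustrative simulation; assumptions, not protocol figures).** Lower IMET is better, so benefit is negative. True 6-month difference -0.44 SD; baseline to 6-month correlation 0.5; 10% random loss by 6 months in each arm; then loss of the 12-month form, bringing the total to about 20% per arm. Where that later loss depends on outcome, carers doing worse at 6 months relative to their own arm's mean are less likely to return the form (log-odds 1.0 per SD). The quantity is the difference between arms in change from baseline to 6 months.

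| 12-month loss depends on outcome in | Complete cases | All observed 6-month values |
|---|---|---|
| CG only | -0.39 | -0.44 |
| Neither arm | -0.44 | -0.44 |
| Both arms alike | -0.44 | -0.44 |
| IG only, half the slope | -0.47 | -0.44 |
| IG only | -0.49 | -0.44 |

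The extremes miss the truth by 0.05 SD, which is 0.05 / 0.44 = 11% in either direction. The last column recovers -0.44 because, by construction, loss up to 6 months was random; all the bias in this set-up comes from deleting 6-month values already collected.

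**Step 4: power as a function of combined loss over both follow-ups.** The protocol gives no combined figure. The assumed range runs from 20% to 36%, the upper end being independent 20% loss at each follow-up: 1 - 0.8 × 0.8 = 0.36. Power is from the noncentral t-test at d = 0.44.

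| Combined loss | Complete cases per arm of 103 | Power | Enrolment per arm to keep 82 |
|---|---|---|---|
| 20% | 82 | 80.0% | 103 |
| 25% | 77 | 77.4% | 110 |
| 28% (20%, then 10% of the rest) | 74 | 75.8% | 114 |
| 30% | 72 | 74.6% | 118 |
| 36% | 66 | 70.8% | 129 |

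**The case against.** The strongest reply has four parts.

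- **Power.** A reader might infer that complete-case analysis must erode the planned 82 per arm. The document does not support this: 103 × 0.8 = 82.4, so 82 is already net of the expected 20%. Nor is that 20% tied to 6 months; the effect sizes are, but the dropout sentence names no time point and could mean total study loss. This part stands. What remains is that the time point is unstated.
- **Bias.** A reader might infer that the result is valid only if loss is completely at random, or that the effect will be overstated. Neither follows. Outcome-dependent loss that is alike in both arms leaves the contrast at -0.44, and control-group-only dependence understates the effect. Nothing in the protocol says that loss will differ by arm, and it cites the carers' loyalty to the clinic. That loyalty bears on how much loss there is, not on whether it is balanced, so the risk remains but its direction and size are unknown.
- **Which waves count.** It is tempting to say that missing any wave removes a carer. For IMET this is wrong, because it is not collected at the end of rehab; four waves apply only to the CES-D, SCL-90-R and WHOQOL-BREF. The section also does not list the occasions in each model. If the primary comparison used baseline and 6 months alone, a missing 12-month form would cost nothing there.
- **Allocation.** A reader might infer an as-treated or per-protocol comparison. None is named, and no attendance threshold is set; complete cases can still be compared as allocated. What is lost is the completeness of the randomised set.

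The reply does not remove the core. Complete-case analysis is a stated rule and not a detail left to an analysis plan, and it is the only handling of missing data that the article states.

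**Conclusion.** The concern holds in limited form. The protocol fixes an analysis that leaves out an expected 21 of 103 carers per arm and, if both follow-ups are in the model, discards 6-month IMET values that were collected. The effect is biased if outcome-related loss differs by arm. Under the assumptions above the 6-month estimate lies between about -0.39 and -0.49 against a true -0.44, with no bias when the dependence is the same in both arms; other assumptions would give other sizes. A power shortfall is not shown. It arises only if combined loss exceeds 20%, and losses of 25% to 36% would leave 77 to 66 per arm and 77% to 71% power.

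**What to change.** Replace the complete-case rule with an analysis of all randomised carers in their allocated arm, using every available 6- and 12-month IMET value in a likelihood-based linear mixed model (SPSS MIXED), with the baseline value as covariate. Keep complete cases as a sensitivity analysis. State whether the 20% dropout refers to 6 months or to the whole follow-up.

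The cost is a change of wording and a little programming in the software already named; recruitment and data collection are unaffected. The model relies on a missing-at-random assumption, so it would not fully correct loss that depends on values never observed, and a carer with neither follow-up value contributes no outcome information.
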